# Single-case experimental designs for bumetanide across neurodevelopmental disorders: BUDDI protocol

**DOI:** 10.1186/s12888-022-04033-8

**Published:** 2022-07-07

**Keywords:** Bumetanide, Autism spectrum disorder, Neurodevelopmental disorders, Children

## Abstract

**Background:**

Bumetanide is a selective NKCC1 chloride importer antagonist which is being repurposed as a mechanism-based treatment for neurodevelopmental disorders (NDDs). Due to their specific actions, these kinds of interventions will only be effective in particular subsets of patients. To anticipate stratified application, we recently completed three bumetanide trials each focusing on different stratification strategies with the additional objective of deriving the most optimal endpoints. Here we publish the protocol of the post-trial access combined cohort study to confirm previous effects and stratification strategies in the trial cohorts and in new participants.

**Method/design:**

Participants of the three previous cohorts and a new cohort will be subjected to 6 months bumetanide treatment using multiple baseline Single Case Experimental Designs. The primary outcome is the change, relative to baseline, in a set of patient reported outcome measures focused on direct and indirect effects of sensory processing difficulties. Secondary outcome measures include the conventional questionnaires ‘social responsiveness scale’, ‘repetitive behavior scale’, ‘sensory profile’ and ‘aberrant behavior scale’. Resting-state EEG measurements will be performed at several time-points including at Tmax after the first administration. Assessment of cognitive endpoints will be conducted using the novel Emma Tool box, an in-house designed battery of computerized tests to measure neurocognitive functions in children.

**Discussion:**

This study aims to replicate previously shown effects of bumetanide in NDD subpopulations, validate a recently proposed treatment prediction effect methodology and refine endpoint measurements.

**Trial registration:**

EudraCT: 2020–002196-35, registered 16 November 2020, https://www.clinicaltrialsregister.eu/ctr-search/trial/2020-002196-35/NL

## Background

Neurodevelopmental disorders (NDDs) are heterogeneous conditions grouped by the DSM-5 as attention deficit hyperactivity disorder (ADHD), autism spectrum disorder (ASD), intellectual disability and learning disorders [1]. The more severe forms often require medicinal interventions but options are currently restricted to symptom suppressing medication. Whereas for ADHD multiple stimulant drugs are registered, for ASD no medication is registered to improve the core defining features but drugs are often prescribed to mitigate associated symptoms such as depression, hyperactivity and irritability.

The advent of genetic animal models of neurodevelopmental conditions has led to the identification of possible mechanism-based treatments, most notably for ASD. One of the most studied options is selective Na^+^-K^+^-2Cl^−^ (NKCC1) antagonist bumetanide. Bumetanide is a registered loop diuretic that has been used for almost 50 years in adults and children with a variety of nephrological and cardiac conditions. Bumetanide has a mild side effect profile with diuretic effects such as electrolyte imbalance and hypokalemia that can be safely monitored when kidney function is normal [2, 3]. Blocking NKCC1 chloride import in the brain can lower chloride concentrations and potentially reinstate GABAergic inhibition. In normal development a developmental sequence occurs around birth, which is characterized by dramatic decrease in chloride concentration in neuronal cells. This maturational downregulation of chloride levels causes a shift in the so-called polarity of GABAergic transmission from excitatory (depolarizing) to inhibitory (hyperpolarizing): as referred to as the GABA-shift. The GABA shift is mediated predominantly by a change in the expression of two chloride co-transporters: the Na-K-2Cl cotransporter isoform 1 (NKCC1) importer and K-Cl cotransporter isoform 2 (KCC2) exporter [4, 5], hence the potential for bumetanide to restore inhibitory GABA signaling. Since GABAergic inhibition has an important role in maintaining E/I balance for proper neuronal growth, and synapse and circuit development, alterations in polarity may have wide-ranging consequences. Indeed, in model studies for ASD [6–8], epilepsy [9], Rett syndrome [10] and Down syndrome [11], the GABA shift was found to be abolished and excitatory effects of GABAergic signaling were established.

These findings lead to the initiation of bumetanide trials in ASD and several genetic disorders, with varying results [6–8]. This is in our opinion, in part the result of ignoring etiological heterogeneity of NDDs, which is likely to result in mechanism-based options not fulfilling a one-size-fits application (as opposed to symptom suppressing treatments). As such, we argue that these treatments will only be effective in a subset of patients with NDDs [2, 12]. Accordingly, we developed a set of trials testing different behavioral neurophysiological and genetic stratifications to evaluate efficacy across different diagnostic classes and to develop strategies for more successful application:

‘Bumetanide for autism medication and biomarker study’ (BAMBI), to replicate effectiveness in ASD on core symptomology and to develop electro-encephalogram (EEG) and cognitive stratification and prediction markers.

‘Bumetanide for the autism spectrum clinical effectiveness trial’ (BASCET), to test effectiveness in a cohort stratified by the presence of sensory reactivity problems across NDDs (ASD, ADHD, epilepsy).

‘Bumetanide for ameliorate tuberous sclerosis complex (TSC) hyper-excitable behaviors’ (BATSCH)’, an open label trial in children stratified by a genetic disorder with previously suggested efficacy of bumetanide.

In these trials, we evaluated multiple outcome levels including: behavior, cognition and neurophysiological changes using questionnaires, neurocognitive testing and resting-state EEG and event-related (ERP) markers, see Tables 1 and 2. The resting-state EEG markers focused on measuring effects on excitation-inhibition (E/I) ratios in line with the putative effect of bumetanide on GABAergic transmission [13]. The main findings included: 1) A superior effect of bumetanide on repetitive behavior in ASD (BAMBI) and TSC (BATSCH) [14, 15], 2) A significant effect of bumetanide on aberrant behaviors across disorders (BASCET and BATSCH), and 3) Enhanced power and excitation-inhibition ratios [13] only in the bumetanide treated group in the BAMBI trial. From the EEG effects, we developed an initial prediction algorithm by incorporating EEG biomarkers and clinical severity scores (RBS-r) [16].

**Table 1 Tab1:** Details of BAMBI, BASCET and BATSCH cohorts

	BAMBI	BASCET	BATSCH
**Trial design**	RCT	RCT	Open label
**Cohort**	Unmedicated ASD	Children with sensory processing difficulties and ADHD/ASD or epilepsy	Children with TSC and behavioral problems
**Age (years)**	7–15	7–15	5–18
**n**	92	50	15
**IQ (mean, (SD))**	101,0 (20,4)	99,2 (24,2)	66,7 (23,9)

*ADHD* attention deficit hyperactivity disorder, *ASD* autism spectrum disorder, *RCT* randomized controlled trial, *TSC* tuberous sclerosis complex

**Table 2 Tab2:** Outcomes of BAMBI, BASCET and BATSCH trials

Domain	Outcome measure	BAMBI	BASCET	BATSCH
**Behavioral outcomes**				
**Social communication and interaction**	SRS-2 (subscales social awareness, social cognition, social communication, social motivation)	X^a^	X	X
**Restricted, repetitive patterns of behavior**	SRS-2 (subscale mannerisms)	X^a^	X	X
	RBS-r	X	X	X
**Aberrant behavior**	ABC	X	X^a^	X^a^
**Sensitivity to sensory stimuli and Sensory stimulation tolerance**	SP-NL	X	X	X
	SP-SC		X	X
	HSP	X	X	
**Quality of life and social improvement**				
**Quality of life**	QoL	X	X	X
	EQ-5D-5L	X	X	X
	EQ-5D-Y	X	X	X
	pedsQL		X	X
**Executive functions**	TRF	X		X
	BRIEF	X		X
**Economic evaluation**	iPCQ	X		X
	TIC-P	X		X
**Disease specific outcomes**				
**TSC**	TAND checklist			X
**Epilepsy**	Epilepsy variables		X	
**Cognitive measurements**				
**Working memory**	Digit span of the WISC-III, spatial span of the Wechsler Nonverbal scale of ability	X		X
**Memory**	Rey auditory verbal learning test, rey visual design learning test	X		X
**Semantic memory**	Recalling sentences subtest of the clinical evaluation of language fundamentals	X		X
**Baseline response speed**	ANT	X		X
**Prepotent response inhibition**	Go-nogo task and condition two of the auditory and visual shifting set tasks of the ANT	X		X
**Attentional flexibility**	Condition three of the auditory and visual shifting set tasks of the ANT	X		X

## Methods/design

The Bumetanide for developmental disorders (BUDDI) study is a post-trial access cohort using Single-Case Experimental Designs (SCEDs) testing bumetanide treatment during 6 months. This type of N-of-1 design is most appropriate for our post-trial access cohort as 1) N-of-1 designs involving placebo treatment periods may not be tolerated, as many participants have already participated in placebo-controlled experiments (i.e. BAMBI, BASCET) and 2) the washout data of BAMBI and BASCET trials suggested prolonged effects of bumetanide treatments, which cause difficulty in placebo versus treatment cross-over designs due to carry over effects. The study will be performed at the N=You neurodevelopmental Precision Center at the Emma Children’s Hospital in the Amsterdam University Medical Center (AUMC), the Netherlands. SCEDs are preferred over the conventional post-trial access design (open label), because of the goals of more individualized effect measurements and improvement of clinical end point selection.

### Design

We will use multiple baseline SCEDs (MBD) in which the intervention (bumetanide) is introduced sequentially to different patients with a baseline period ranging from 2 to 12 weeks. The rationale for this multiple baseline is that apart from clinical and response heterogeneity across individuals also symptoms per patient vary over time. In an MBD the variation in the baseline period (A phase) is compared to the variation during the intervention (B phase) on an individual level (i.e. the participant serves as his/her own control). Evidence of such an AB designs is based on demonstrating that the change in behavior only occurs during intervention.

### Study population

All participants that participated in the previous studies, as well as a new cohort with matching inclusion and exclusion criteria are eligible for this post-trial access study. See Table 3.

**Table 3 Tab3:** In- and exclusion criteria BUDDI trial

Inclusion criteria	Exclusion criteria
1. Inclusion in BAMBI, BASCET or BATSCH trial; 2. Written informed consent Or 1. Males or females aged ≥7 years to ≤17 years; 2. One of the following: 3. Above clinical cut-off scores of altered sensory reactivity on the Sensory Profile and either a clinical ASD or ADHD diagnosis based on DSM-5 (or DSM-IV) or an epilepsy diagnosis, 4. Criteria met for autism on DSM-IV or V and Social Responsiveness Scale (SRS-2) 5. A history of behavioral problems combined with a definite diagnosis of TSC: either meeting criteria for clinical definite TSC, or a mutation identified in the TSC1 or TSC2 gene; 6. Written informed consent	1. Inability to comply with the protocol-specified procedures for the duration of the study, including treatment, blood sampling to control diuretic effects; a. This does not include inability to perform neurocognitive testing due to intellectual disability, as there is no minim IQ needed. 2. Presence of a severe medical or genetic disorder other than related to ASD, TSC or epilepsy; 3. Serious, unstable illnesses including, gastroenterological, respiratory, cardiovascular (arrhythmias, QT interval lengthening), endocrinologic, immunologic, hematologic disease, dehydration or hypotension, electrolyte disturbances (Na < 133 mmol/L, K < 3.5 mmol/L or Ca < 2.17 mmol/L (<13y) or < 2.2 mmol/L (>13y); 4. Renal insufficiency (CKD st2–5; estimated glomerular filtration rate < 90 ml/min/1.73 m2), congenital or acquired renal disease with decreased concentration capacity (tubulopathy, diabetes insipidus) and liver insufficiency interfering with excretion or metabolism of bumetanide; 5. Start of behavioral treatment during study; 6. Treatment with psychoactive medications, including antipsychotics and AEDs, **except** methylphenidate, is allowed if on a stable regime in terms of types and dosage from 2 months prior to the study to the end of the study; 7. Treatment with NSAIDS, aminoglycosides, digitalis, antihypertensive agents, indomethacin, probenecid, acetazolamide, Lithium, other diuretics (e.g., furosemide, hydrochlorothiazide), drugs known to have a nephrotoxic potential; 8. Documented history of hypersensitivity reaction to sulfonamide derivatives; 9. Body weight < 30 kg (for reason of dosing).

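### Eligibility sets no bumetanide-free interval, although the protocol itself reports prolonged drug effects, so recently exposed returners could bring residual effect into the baseline phase

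*Protocol article*

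**What the plan says.** Under Methods/design the protocol explains why it does not alternate placebo and drug: "the washout data of BAMBI and BASCET trials suggested prolonged effects of bumetanide treatments". It treats this carry-over as an obstacle to a cross-over comparison.

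Under Study population it states: "All participants that participated in the previous studies, as well as a new cohort with matching inclusion and exclusion criteria are eligible". In Table 3 the route for former participants reads, in full, "1. Inclusion in BAMBI, BASCET or BATSCH trial; 2. Written informed consent". Exclusion 7 bars several drug classes, ending with "other diuretics (e.g., furosemide, hydrochlorothiazide" and nephrotoxic drugs; bumetanide is not named. The one time window for medication, in exclusion 6, asks for a "stable regime in terms of types and dosage from 2 months prior to the study to the end of the study" and concerns psychoactive drugs. The registration data set in Appendix 3 gives no interval since bumetanide either.

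The Design section makes the A phase, 2 to 12 weeks long, each child's own control, and says: "Evidence of such an AB designs is based on demonstrating that the change in behavior only occurs during intervention". Under Data analysis, the 2-SD band is computed from the baseline scores and the interrupted time series analysis (ITSA) forecasts from them.

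**The concern.** Carry-over is the protocol's stated reason for not using a cross-over. A baseline-first design avoids carry-over that arises within the study, but not carry-over brought in from an earlier one. For a child exposed shortly before consent, the A phase would be a period of fading drug effect and not an untreated comparator, and change confined to the B phase could not be shown.

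Four uses of the data depend on this: the individual 2-SD verdict, the group estimate, the EEG at Tmax after the first dose, and the evaluation of the EEG-based predictor, where a responder with a contaminated baseline could be labelled a non-responder. The Selection bias section expects earlier responders to be over-represented, and these are the children in whom residual effect is most plausible. Its two remedies, a responder covariate and inverse probability weighting, address who enters. Neither uses time since last dose, so neither removes residual drug effect.

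**Working it through.** **Inputs from the protocol.** Baselines of 2 to 12 weeks in 11 equally frequent lengths (Randomization). At least 75 returners and 40 new children, so 75/115 = 65% (Power calculations). Planning effect d = 0.4, with stated power 0.71 at N = 40 and 0.73 at N = 50 without autocorrelation, and 0.69 at N = 60 with r = 0.3.

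**Not given, so assumed.** Decay of the effect, time since last dose, share of children exposed, and measurement frequency (taken as weekly).

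**1. The plan's power figures.** A two-sided 5% normal approximation gives Φ(0.4·√40 − 1.96) = Φ(0.57) = 0.716 at N = 40, close to 0.71. At N = 50 it gives Φ(0.87) = 0.807, not 0.73. Alpha, sidedness and number of measurements are not stated, so this is not a fair reproduction, and I do not call the stated figures wrong. They serve only as a reference.

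**2. Residual share of the effect in the baseline.** With full effect at the last dose, half-life h weeks, a drug-free gap of g weeks before baseline and baseline length L, the share is the mean over t = 1…L of 0.5^((t+g)/h), then averaged over L = 2…12.

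| Gap before baseline | h = 2 | h = 4 | h = 8 |
|---|---|---|---|
| 0 weeks | 0.35 | 0.55 | 0.73 |
| 8 weeks | 0.02 | 0.14 | 0.36 |
| 52 weeks | 0.00 | 0.00 | 0.01 |

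The last entry is 0.73 × 0.5^(52/8) = 0.008. With h = 4 and no gap, a 2-week baseline retains (0.84 + 0.71)/2 = 0.77 and a 12-week baseline 0.39. The contamination is therefore tied to the randomised baseline length and is not a constant offset.

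**3. Effect on power.** Let p be the share of children exposed and c the share of effect retained through the A phase. The mean contrast becomes 0.4·(1 − p·c). As an upper bound, p = 0.65 treats every returner as recently exposed.

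- c = 0.5: 0.4 × (1 − 0.325) = 0.27. Normal-approximation power at N = 115 falls from 0.99 to 0.83.
- c = 1: 0.4 × 0.35 = 0.14, power 0.32.
- p = 0.33 (about half the returners) with c = 0.5: 0.334, power 0.95.

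A simulated multiple-baseline randomization test (38 weekly scores, effect in within-child SD units, 100 permutations, 400 replicates) gives:

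| Scenario (p = 0.65 where exposed) | N = 115, r = 0 | N = 60, r = 0.3 |
|---|---|---|
| No carry-over | 0.98–0.99 | 0.78–0.82 |
| Constant, c = 0.5 | 0.83 | 0.51 |
| Constant, c = 1 | 0.41 | 0.23 |
| Full at start, 4-week half-life | 0.94 | 0.62 |

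The ranges are repeat runs; Monte Carlo standard error is about 0.02 or less. The decaying case loses less power than its mean residual share of 0.55 suggests. The test compares the observed contrast with contrasts at other start weeks, not with zero.

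**4. Direction in the other analyses.** Take a 12-week baseline, h = 4 and no gap. The residual falls from 0.84 of the effect in week 1 to 0.125 in week 12.

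- A flat forecast at the baseline mean leaves 1 − 0.39 = 0.61 of the true effect.
- A straight line through the end points falls (0.84 − 0.125)/11 = 0.065 per week and reaches the untreated level 0.125/0.065 = 1.9 weeks after the last baseline score. Beyond that the forecast is worse than untreated, and the effect is overstated.
- For the 2-SD band, the centre moves toward the treated level by 0.39 of the effect. The drift also adds to the baseline SD. At an effect of 0.4 within-child SD the widening is negligible (drift SD 0.23 × 0.4 = 0.09, and √(1 + 0.09²) = 1.004). It grows with the effect relative to a child's week-to-week variation.

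**The case against.** The strongest reply is that recent exposure is nowhere shown. The abstract says "we recently completed three bumetanide trials each focusing on different stratification strategies". Two of the three were randomised with placebo periods, and both have washout data, so off-drug follow-up had already taken place. Only BATSCH (15 children) was open label. If a year or more has passed, the residual is practically nil. All of this stands, and it means that p is probably well below 0.65.

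A reader might infer that children still taking bumetanide will pass through the baseline on drug, with an expected A-to-B contrast near zero. The documents do not support that. The Design section introduces the drug after baseline, the intervention section describes a starting dose for all participants, and the EEG at Tmax follows a first dose. All three presuppose children who are off drug when the B phase starts. Table 3 merely fails to say so.

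A reader might also infer that carry-over always hides the effect, or that the trial is underpowered. Neither follows. ITSA can err either way, and the planned modelling of trends may absorb part of a drift. At N = 115 even the upper-bound share with a 4-week half-life leaves simulated power at 0.94.

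Finally, last-use dates and analysis sets may be in the full protocol or the statistical analysis plan, and the safety checks already ask about other medication. That is fair for the analysis set. It is weaker for eligibility: Table 3 is a detailed list, down to electrolyte limits and a 2-month stability window, and it names no bumetanide interval.

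**Conclusion.** The point holds as a gap between the protocol's own statement of prolonged effects and its entry criteria. It is not a demonstrated bias. For any child exposed shortly before consent, the baseline would carry a residual effect that depends on the randomised baseline length: 35% to 73% of the effect on average, under assumed exponential decay with half-lives of 2 to 8 weeks. With a year or more off drug it is below 1%. Mean contrasts and the randomization test would be weakened; ITSA could be biased either way. Large power losses require that most returners be recently exposed and that the residual hardly fade. Without the exposure date, neither the sponsor nor a reader can tell which case applies. The change is worth making because it is cheap and because the protocol itself names the hazard.

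**What to change.** Record the date of last bumetanide use for every participant at screening. For children already enrolled (the registration data set gives first enrolment as December 2020), retrieve it from the earlier trial records and the caretakers.

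Before analysis, pre-specify a minimum bumetanide-free interval before the first A-phase score, justified from the BAMBI and BASCET washout data that the sponsor holds. Then do one of two things:

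- restrict the group efficacy, first-dose Tmax EEG and predictor analyses to children beyond that interval; or
- keep all children in the main analysis and run that restriction as a pre-specified sensitivity analysis, with time since last dose as a covariate.

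In either case, report recently exposed children separately. The interval defines an analysis set only: no child is refused post-trial access or asked to stop a treatment. The cost is one screening item, one line in the criteria or analysis-set definition, and possibly a few fewer children in the efficacy set.

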### Recruitment and screening

All previous participants of the BAMBI, BASCET and BATSCH trials will be contacted and informed about this post-trial access study. If interested and eligible, previous participants will receive verbal and written information about the study. We estimate that 50% of the patients that were enrolled in the three previous bumetanide trials will be eligible and motivated to be enrolled in the present study (i.e., 75 patients in total).

Participants of the new cohort will be recruited from the patient population referred to the N=You neurodevelopmental Precision Center at the Emma Children’s Hospital in the AUMC.

### Intervention and preparation of study drugs

The intervention constitutes of bumetanide tablets. Bumetanide will be provided at a starting dose of 0.5 mg twice daily and will be increased to the therapeutic dosage of 1.0 mg twice daily at day 7 if there are no signs of dehydration in all participants. In case of limited effects and side-effects and a weight > 45 kg dosage can be increased to 1.5 twice daily. Dose reductions to manage side effects will be allowed at any time. Tablets will be obtained via the research pharmacy of AUMC. Re-labeling will be prepared and applied according to local regulatory requirements (GMP annex 13 guidelines). Participants are instructed to return unused tablets to allow monitoring of drug adherence.

